# Effect of Early Treatment of Spasticity After Stroke on Motor Recovery: Protocol for the Baclotox Multicenter, Double-Blind, Double-Dummy Randomized Controlled Trial

**DOI:** 10.2196/62951

**Published:** 2025-05-09

**Keywords:** stroke, rehabilitation, muscle spasticity, botulinum toxin A, baclofen, hemiplegia, motor recovery

## Abstract

**Background:**

Individuals with poststroke hemiplegia often develop spasticity, which increases disability. Antispastic treatments such as baclofen and botulinum toxin are commonly prescribed in poststroke recovery. However, their impact on motor recovery, especially when administered within the first 2 months after stroke, remains unclear.

**Objective:**

This study aims to compare the motor recovery effects of botulinum toxin versus oral baclofen. The hypothesis is that botulinum toxin is more supportive of motor recovery than baclofen and enhances functional recovery.

**Methods:**

The study is a multicenter, controlled phase IV, comparative, prospective, randomized, double-blind, double-dummy, superiority trial to compare the toxin and baclofen, and a noninferiority trial to compare the toxin and the placebo. It focuses on the time course of the Fugl-Meyer Motor Assessment (FMA) as the primary outcome. The main inclusion criterion is patients with a single stroke in the past 2 months. Treatment comprises 1 intramuscular injection at treatment initiation and oral tablets for 4 months. Randomized patients are allocated to 3 arms: botulinum toxin with placebo baclofen, baclofen with placebo botulinum toxin, and placebo baclofen with placebo botulinum toxin. FMA scores are assessed at pretreatment, 1 month, and 3 months later. Spasticity, functional abilities, activities of daily living, pain, and quality of life are also evaluated. Adverse effects are monitored. A positive difference of 13 points in the FMA time course between the botulinum toxin and baclofen groups is considered a relevant effect. The data analysis plan involves linear regression models to compare primary and secondary outcomes, with adjustments for covariates such as age, center, and associated treatments. Subgroup analyses will examine proportional recovery profiles, and missing data in Fugl-Meyer scores will be addressed using imputation methods.

**Results:**

A total of 179 participants were randomized across 18 centers, with inclusions delayed due to the COVID-19 pandemic. As of December 2024, the data manager currently has all the data, and a review of data quality is in progress. No statistical analysis has been conducted so far, and the blind will be lifted after the analysis.

**Conclusions:**

This study identifies the most suitable spasticity treatment, considering the specificities of the stroke and constraints during the recovery phase. It will provide recommendations for the primary treatment of early spasticity post stroke.

**Trial Registration:**

ClinicalTrials.gov NCT02462317; https://clinicaltrials.gov/study/NCT02462317; European clinical trials (EudraCT) 2010-022881-28; https://www.clinicaltrialsregister.eu/ctr-search/trial/2010-022881-28/FR

**International Registered Report Identifier (IRRID):**

DERR1-10.2196/62951

Baclofen is a GABA (γ-aminobutyric acid)-B agonist that reduces spasticity by enhancing presynaptic inhibition, thereby decreasing the excitability of afferents in spinal reflexes. Despite its widespread use and endorsement by the French National Health Authority, Haute Autorité de Santé, as a first-line treatment, studies in animal models have raised concerns about the impact of GABAergic drugs on motor recovery. Research indicates that GABAergic agents, such as diazepam, can impair motor recovery and brain plasticity postinjury [10,11]. Baclofen has shown similar detrimental effects on visuomotor learning in healthy human participants, suggesting a potential risk for individuals undergoing motor recovery post stroke [12]. However, the absence of direct studies on baclofen’s effects during the recovery phase post stroke leaves a critical gap in understanding its impact on motor outcomes.

Botulinum toxin A, meanwhile, acts by blocking acetylcholine release at the neuromuscular junction, thereby temporarily paralyzing targeted muscle fibers and reducing spasticity [13]. Its effects generally become noticeable within days and persist for approximately 4 months [14]. Randomized controlled trials demonstrate botulinum toxin’s effectiveness in reducing spasticity in patients with chronic stroke; yet, its effects on motor function are less clear [9,13,15,16]. Most studies have focused on its use in the chronic phase over 6 months post stroke, a period when plasticity decreases and muscular changes may be irreversible. Notably, research using transcranial magnetic stimulation and functional magnetic resonance imaging indicates that botulinum toxin injections may have modulatory effects on the central nervous system, potentially enhancing brain plasticity and supporting recovery [17-21]. This evidence suggests that early use of botulinum toxin in the subacute phase could offer motor recovery benefits by influencing neuroplastic processes.

Given the limited understanding of how these treatments affect motor recovery in the subacute phase, this study aims to investigate the comparative efficacy of baclofen and botulinum toxin A on motor recovery post stroke. Our hypothesis is that botulinum toxin will demonstrate a superior effect on motor recovery compared to baclofen, as it may mitigate spasticity without the potential negative effects on plasticity observed with GABAergic drugs.

### Objectives

#### Main Objective

This study aims to demonstrate the superiority of botulinum toxin A over baclofen on motor recovery in the subacute phase after stroke. The primary end point is the change in the Fugl-Meyer Assessment (FMA) motor score from the start of treatment to 3 months later.

#### Secondary Objectives

Our secondary objectives are as follows:

To compare the effects of botulinum toxin A and placebo on motor recovery (FMA) over 3 months and establish clinical equivalence.To evaluate the impact of treatment on motor recovery (main objective and placebo comparison) based on initial FMA-upper extremity (FMA-UE) scores.To assess changes in motor recovery (FMA) during the first month of treatment.To compare the effectiveness of the treatments in reducing spasticity symptoms over 1 and 3 months using the Tardieu Scale and Modified Ashworth Scale (MAS).To evaluate functional improvement 3 months after treatment using the Rivermead Motor Assessment (RMA), Rankin score, and Barthel score.

#### Exploratory Objectives

To assess the impact of treatments on pain using a visual analog scale (VAS) at 1 and 3 months.To evaluate the quality of life over 3 months using the Reintegration to Normal Life Index (RNLI), a scale validated for patients with vascular hemiplegia.To compare reaction times at baseline, 1 month, and 3 months to investigate cognitive effects of treatment.To measure patient satisfaction with treatment at 1 and 3 months.

## Methods

### Study Design

This is a multicenter, controlled phase IV, comparative, prospective, randomized, double-blind, double-dummy, superiority trial to compare the toxin and baclofen, and a noninferiority trial to compare the toxin and the placebo. Because of the different modes of administration of these treatments, each group receives both an injection and oral tablets. The study therefore comprises three arms: (1) a “toxin” group treated with an injection of botulinum toxin and placebo oral baclofen; (2) a “baclofen” group treated with oral baclofen and an injection of placebo botulinum toxin; and (3) a double “placebo” group treated with placebo oral baclofen and an injection of placebo botulinum toxin. The CONSORT (Consolidated Standards of Reporting Trials) flowchart in Figure 1 summarizes the enrollment and allocation of the participants.

All patients, regardless of their assigned group, benefit from daily neurorehabilitation care. This care starts simultaneously with the initiation of treatment. For each patient, the protocol duration spans 4 months: 3 months of the controlled protocol and 1 month of gradual discontinuation of the tablets. This gradual discontinuation reflects the standard procedure for stopping baclofen. Participants are recruited from the 18 French physical medicine and neurorehabilitation hospital wards participating in this protocol. The list of study sites can be found in Multimedia Appendix 1.

The SPIRIT (Standard Protocol Items: Recommendations for Interventional Trials) guidelines resume the intervention and assessments of the study (Figure 2).

This study is registered in the European EudraCT database (2010-022881-28) and is also registered in ClinicalTrials.gov (NCT02462317).

**Figure 1 figure1:**
[figure not shown]
CONSORT (Consolidated Standards of Reporting Trial) flow diagram. mITT: modified intention-to-treat; PP: per-protocol; V1: visit 1; V2: visit 2; V3: visit 3.

**Figure 2 figure2:**
[figure not shown]
SPIRIT (Standard Protocol Items: Recommendations for Interventional Trials) schedule of enrollment, interventions, and assessments. FMA: Fugl-Meyer Assessment; RMA: Rivermead Motor Assessment; RNLI: Reintegration to normal life; V0: allocation visit; V1: visit 1; V2: visit 2; V3: visit 3; VAS: visual analog scale.

### Ethical Considerations

This study received Ethics Committee approval (CPP Sud-Ouest et Outre-Mer II) on March 23, 2015 (review number 2-14-33) and authorization from the Agence Nationale de Sécurité du Médicament (ANSM) on December 29, 2014. Conducted in accordance with the Declaration of Helsinki, the study requires both oral and written informed consent from participants. During the preinclusion visit, the investigating physician explains the study’s objectives, procedures, potential risks, benefits, and patient rights. Each participant receives an information sheet and consent form, followed by a minimum 48-hour reflection period to decide on participation. An ancillary study is carried out in the main investigating center. The patient is given a different consent form for this ancillary study and is provided with comprehensive information. In line with the French Public Health Code (articles L.1121-3 and R.5121-13), confidentiality is strictly maintained. Collected data are anonymized, with patient codes generated from initials and inclusion numbers, which are linked only to the center and enrollment order. The sponsor ensures that all participants consented to data access solely for quality assurance. No financial or material compensation was provided; participation was voluntary without incentives.

### Participants

#### Eligibility Criteria

##### Inclusion Criteria

The inclusion criteria are as follows:

Man or woman between the ages of 18 and 80 years.First ischemic or hemorrhagic stroke resulting in hemiplegia.Sufficient understanding to participate in the study: Boston Diagnostic Aphasia Examination>3.The stroke occurred less than 2 months ago.Presence of spasticity warranting treatment: Tardieu score>1(≥2) in one of the following muscle groups: triceps sural, wrist flexors, finger flexors, and elbow flexors.The patient’s consent was obtained.Affiliated with a social security scheme or equivalent.

The inclusion criteria ensure that participants represent the target population most likely to benefit from the intervention, including adults with recent first strokes and spasticity warranting treatment. These criteria also confirm their capacity to engage meaningfully in the study through sufficient cognitive understanding and access to standard rehabilitation care.

##### Exclusion Criteria

The exclusion criteria are as follows:

Renal failure at the time of inclusion.Currently on antispastic therapy: baclofen, dantrolene, and tizanidine.A history of botulinum toxin injection.A history of traumatic or vascular brain injury, myasthenia gravis, Lambert Eaton syndrome, or neuromuscular disease.PregnancySurgery with curare within the last monthTreatment with aminoglycosides, aminoquinolines, or cyclosporine.Progressive disease at the time of inclusion.A history of convulsive seizure or taking antiseizure medication.A history of psychosis or neuroleptic treatment.Liver function test abnormalities, at the investigator’s discretion.Blood count abnormalities, at the investigator's discretion.A history of intolerance or allergic reaction to lactose.Glucose or galactose malabsorption syndrome and lactase deficiency.A history of anaphylactic reaction.Inability to undergo daily rehabilitation for 2 hours.Under guardianship, curatorship, safeguard of justice.Receiving anticoagulant treatment: heparin with an electric syringe or antivitamin K at an effective dose.

The exclusion criteria are designed to ensure participant safety and the validity of the study by excluding individuals with medical conditions, treatments, or histories that could compromise the intervention’s safety or effectiveness. Participants unable to follow the study protocol are also excluded. These criteria include the standard exclusions for Botulinum toxin treatment and oral baclofen therapy.

### Study Center Inclusion Criteria

Study centers must have experience in spasticity assessment and conducting botulinum toxin A injections. They must admit an adequate number of patients post stroke in the subacute phase for hospitalization every year.

Participants are recruited from among the outpatients and inpatients of the physical and neurorehabilitation medicine ward. Two or more experts determine eligibility according to the inclusion and exclusion criteria.

### Intervention

At the allocation visit (V0), the investigator administered the intramuscular injections and prescribed the tablets. The tablets were taken daily for 3 months until the second postallocation visit (V2). The dosage of tablets was then gradually decreased over 1 month and the effects were monitored during the close-out visit. All participants also received at least 2 hours of neurorehabilitation daily, 5 days per week, led by specialized therapists. This regimen included both physiotherapy and occupational therapy to support comprehensive motor recovery in accordance with the routine practices of the neurorehabilitation centers.

#### Botulinum Toxin Injection Protocol

The choice of muscle groups to be injected depended on the investigator’s clinical examination. The muscle group that validated the patient’s inclusion (Tardieu>1) was systematically injected. Other muscle groups that met the specific criteria (Tardieu score1) were also systematically injected: the triceps surae, flexor digitorum superficialis, flexor digitorum profondus, flexor carpi radialis, flexor carpi ulnaris, and the brachialis (Multimedia Appendix 2). The maximum total dose permitted is 500 units. Additional muscle groups were injected based on the remaining dose of toxin [22].

Injection site localization was tracked using electrostimulation sometimes combined with muscle ultrasound. Depending on the muscles injected, 1 or 2 injection points would be considered at sites with the highest density of motor endplates. The total number of injection points could range between 15 and 20. If requested by the patient, an analgesia protocol with class II analgesics (paracetamol, codeine, and hydroxyzine) was administered 2 hours prior to the procedure, along with inhalation of an equimolar mixture of oxygen and nitrous oxide (Meopa). This was the standard procedure for toxin injections in the participating centers.

#### Baclofen Intake Protocol

Baclofen was provided in a 10 mg capsule and the chosen dose was 60 mg per day in 3 doses commonly used with success in baclofen studies [9]. Treatment was initiated at a dosage of 10 mg in the evening (1 capsule). The dosage was then increased by 1 tablet (10 mg) every 4 days until a dosage of 60 mg per day was reached. If excess sedation occurred during dosage escalation, the clinician reverted to the previous level for an additional 3 days. After 2 unsuccessful attempts to increase the dosage, the last tolerated dosage was maintained throughout the study. Abrupt discontinuation of treatment was not recommended. On completion of the protocol, the baclofen dosage was gradually reduced by 10 mg (1 capsule) every 3 days.

Exiting the protocol occurred either by the patient’s deliberate choice or by necessity, according to the investigator's decision, in the following circumstances.

Nonadherence to study conditions: poor compliance with the treatment, unauthorized use of other medications.Uncontrolled painful spasticity despite the use of class I and II analgesics.Occurrence of a serious adverse effect or event.

Premature discharge may be warranted in the event of a clinically significant adverse effect, such as mental confusion, severe sedation, swallowing difficulties necessitating discontinuation of oral feeding and insertion of a nasogastric tube, leuconeutropenia, or drug-induced hepatitis revealed by the laboratory tests (1-month visit). On study discharge, the patient was promptly referred to the investigator for follow-up consultations and ongoing management.

To ensure compliance, drug blister packs were collected, and the remaining capsules were counted.

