##### Pain via VAS

Changes in pain were evaluated using a VAS from the allocation to 1 month later (V0 to V1) and from the allocation to 3 months later (V0 to V2).

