### Statistical Methods

#### Statistical Methods for Primary and Secondary Outcomes

The baseline characteristics of the participants are described for the 3 treatment groups and the pairwise standardized differences are used to compare the distribution of baseline covariates between treatment groups.

The variation in the Fugl-Meyer score between the “toxin” and “baclofen” groups is compared using linear regression models. First, the model contains the treatment group as the explanatory variable and the Fugl-Meyer delta score as the response variable. The adjusted model then incorporates the patient’s age, the center, and any associated treatment as explanatory variables, in addition to treatment. The associated treatment is represented by a binary variable indicating the use of at least 1 serotonin reuptake-inhibiting antidepressant (yes or no) or at least 1 benzodiazepine (yes or no). This list is validated during the descriptive analysis of concomitant treatment.

The primary objective tests the superiority of the “toxin” versus “baclofen” in motor recovery at 3 months using 2-sided tests at a 5% α level. The secondary objective aims to demonstrate the clinical equivalence of the “toxin” versus the “placebo” in motor recovery after 3 months, using a 1-sided noninferiority test at a 5% α level and a margin of 13 FMA points to assess noninferiority.

To assess the efficacy of these treatments on spastic symptoms (MAS, Tardieu angle, and Tardieu Scale), 2-tailed *t* tests at a significance level of 5% are conducted for pairwise comparisons. The first analysis is carried out on all muscle groups, and a second analysis is carried out on the muscle groups that have been injected.

For the FMA at 1 month and the variation score between allocation and the second postallocation visit which consists of the RMA the Barthel Index, the Rankin score, the reaction time, satisfaction, pain, and the RNLI, the analyses will be descriptive using the usual statistical measures in each group with a 95% CI.

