#### Methods to Handle Missing Data

The primary and secondary outcomes involve examining the difference in a quantitative variable measured at 2 distinct time points. Since the measurements are based on quantitative longitudinal scores, we use the CopyMean approach in the R software (R Foundation for Statistical Computing) [43]. The specific methodology details are determined after assessing the structure of the missing data (such as monotone patterns). Consequently, with this method, scores at the 3 targeted times will be imputed, and subsequently, differences from the initial measurement will be computed. This methodology is only applied to the FMA, the FMA-UE, and the FMA-LE. Other missing data are not imputed.

Details regarding oversight, monitoring, auditing, and protocol amendments are provided in Multimedia Appendix 3.

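### Exit for uncontrolled painful spasticity can make MAS and Tardieu values missing because of the state they measure, and the plan tests only the values that remain

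*Protocol article*

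**What the plan says.** - **Exit.** Under Baclofen Intake Protocol: "Exiting the protocol occurred either by the patient’s deliberate choice or by necessity, according to the investigator's decision". One of the listed circumstances is "Uncontrolled painful spasticity despite the use of class I and II analgesics". Others are nonadherence and serious adverse effects. The section then says: "On study discharge, the patient was promptly referred to the investigator for follow-up consultations and ongoing management".
- **Objective.** A secondary objective is "To compare the effectiveness of the treatments in reducing spasticity symptoms over 1 and 3 months", with the Tardieu Scale and the MAS. Pain is an exploratory objective: "Changes in pain were evaluated using a VAS" at the same two visits.
- **Analysis.** Under Statistical Methods for Primary and Secondary Outcomes, two-tailed "tests at a significance level of 5% are conducted for pairwise comparisons" of MAS, Tardieu angle and Tardieu Scale, first on all muscle groups and then on the injected ones. Pain is only described per group, with a 95% CI.
- **Missing data.** After describing CopyMean imputation, Methods to Handle Missing Data says: "This methodology is only applied to the FMA, the FMA-UE, and the FMA-LE. Other missing data are not imputed".
- **Population.** All objectives use the modified intention-to-treat set, which requires some assessment after randomization.
- **Exit reasons.** Data Collection and Management says that discontinuations are recorded with their reason.

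**The concern.** The state that permits exit is close to the state that MAS and Tardieu are meant to measure. Where exit stops assessment, the later value is absent because the result was poor, and the stated rule then compares arms without it. This is a positive decision in the article, not a detail left to an analysis plan.

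If an active drug reduces spasticity, more patients on double placebo should reach the exit criterion. Losing them makes placebo look better and narrows the toxin-placebo and baclofen-placebo differences. Between toxin and baclofen, the less effective drug would lose more of its failures, and the two would look more alike.

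At stake is a formally tested secondary conclusion. The rule on unimputed data does not reach the primary FMA comparison, and the exit criterion itself is not in question.

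**Working it through.** **No figure to reproduce.** The article states no exit rate, no effect size and no power for spasticity. Its one stated power for a placebo comparison with missing data concerns the FMA: 108 against 54 patients after 10% loss, SE = 30 × √(1/108 + 1/54) = 5.0, power = Φ(12/5.0 − 1.645) = 77.5% against 77.6% stated. It reproduces, but does not bear on this point.

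**Assumptions (none is in the article).** The change score is normal with SD 1, and higher is worse. Its mean is 0 on placebo and −0.5 on active drug. A patient exits above one threshold *c*, the same in both arms. Placebo exits are 5%, 10% or 15%. An exited patient has no later value.

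**Formulas.**
- Threshold: *c* = z(1 − placebo exit rate).
- Active exit rate: 1 − Φ(*c* + 0.5).
- Improvement in an arm's mean when its worst patients are removed: s(z) = φ(z)/Φ(z), with z = *c* on placebo and *c* + 0.5 on active.
- Observed difference: 0.5 − r × [s(placebo) − s(active)], where r is the correlation between what drives exit and the measured change.

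| Placebo exits | *c* | Active exits | s placebo | s active | Gap | Observed, r = 1 | Loss | Observed, r = 0.6 | Loss |
|---|---|---|---|---|---|---|---|---|---|
| 5% | 1.645 | 1.6% | 0.109 | 0.041 | 0.068 | 0.432 | 14% | 0.459 | 8% |
| 10% | 1.282 | 3.7% | 0.195 | 0.085 | 0.110 | 0.390 | 22% | 0.434 | 13% |
| 15% | 1.036 | 6.2% | 0.274 | 0.131 | 0.144 | 0.356 | 29% | 0.414 | 17% |

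The r = 0.6 columns keep the exit rates shown, so treatment is taken to move the exit driver by the full 0.5 SD. If it moves the driver only by 0.6 × 0.5 = 0.3 SD, s active becomes 0.062, 0.121 and 0.180. The losses are then 0.6 × 0.047/0.5 = 6%, 0.6 × 0.074/0.5 = 9% and 0.6 × 0.095/0.5 = 11%.

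**Wider range.** A simulation with 2,000,000 patients per arm used the same common threshold, with treatment moving the driver by r times the effect. It covered effects of 0.3, 0.5 and 0.8 SD, placebo exits of 5%, 10% and 20%, and r of 1.0, 0.7 and 0.4. The difference shrank in all 27 scenarios, by 2% to 37%.

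**Other exits, starting from 5% placebo exits, r = 1 and a true 0.50 SD.** Adding 10% random adverse-event exits on active drug left the observed difference at 0.43 SD. Adding 15% adverse-event exits concentrated in poor responders on active drug gave 0.55 SD, so the direction reversed.

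**Head count.** With 179 randomized 2:2:1, placebo has about 179/5 ≈ 36 patients. Exit rates of 5% to 15% are about 2 to 5 people.

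**The case against.** The case against has real substance.

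- **Exit is permitted, not automatic.** A reader might infer that treatment failures are removed by rule. The text leaves exit to the patient or the investigator, and nowhere says that the 1-month and 3-month assessments stop. It speaks of study discharge and clinical follow-up, which implies loss of assessments but does not state it.
- **Some data survive.** A patient who leaves after the 1-month visit keeps that value and stays in the modified intention-to-treat set. Only an exit before that visit without any assessment removes the patient altogether.
- **Net direction is open.** A reader might conclude that antispastic effects will be understated. Sedation, confusion and other adverse effects are also grounds for exit, plausibly more often on active drug, and those gaps are not imputed either. The 0.55 SD result above shows that they can reverse the sign.
- **Larger losses need mismatched rates.** Pairing 15% placebo exits with 3% toxin exits gives a 41% loss. Under one threshold those rates imply a shift of 1.881 − 1.036 = 0.84 SD, which does not fit an effect of 0.5 SD.
- **Pain and resistance to stretch differ.** The criterion is pain uncontrolled by analgesics, while the tested outcomes are resistance and angle over several muscles. A correlation of 1 is therefore an upper case.
- **Pain is not tested.** It is exploratory and descriptive, so no test of pain exists to be biased.
- **Worst rank everywhere would overreach.** It would score a patient who left because of one muscle group as worst in all.

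All of this stands, and it limits the size, the certainty and the remedy. The general defence that an article leaves sensitivity analyses to the full plan does not dispose of the point, because the article itself fixes the rule for missing non-FMA data.

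**Conclusion.** The point holds as one mechanism acting on the MAS and Tardieu comparisons. Where exit for uncontrolled painful spasticity ends assessment, missingness depends on the outcome, and the stated analysis makes no allowance for it. Taken alone, the mechanism tends to shrink the differences from placebo: by about 14% to 29% if exit follows the measured change exactly, and by about 8% to 17% at a correlation of 0.6. It is less if treatment acts on the exit driver only through the measured change.

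These sizes rest wholly on the assumed 0.5 SD effect, common threshold and 5% to 15% placebo exits. If few patients left for this reason, the effect is small. The documents do not support a claim that the net spasticity result will be understated, that the primary FMA result is affected through this rule, or that a pain comparison is biased. A supportive analysis is warranted; replacing the main test is not.

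**What to change.** Keep the observed-case t tests as planned. In Statistical Methods for Primary and Secondary Outcomes and in Methods to Handle Missing Data, add the following before unblinding. Preferably fix it before any result is seen by coded group, since the Blinding section notes that the placebo group may be recognised by its size.

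1. A supportive analysis of the MAS and Tardieu comparisons in which exit for uncontrolled painful spasticity counts as an unfavourable outcome at visits after the exit only. Use a failure composite, or worst rank confined to the affected or injected muscle groups. Observed 1-month values stay in place. Say that patients who left for this reason before any assessment are included here, since the modified intention-to-treat definition would otherwise drop them.
2. A table of this exit reason by arm, beside the spasticity results.
3. The same exits shown with the descriptive pain results, without a formal test.

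No new data are needed, because exit reasons are already recorded, and the exit criterion is untouched. The article reports that no analysis had been done by December 2024; if analysis has since begun, label the addition as post hoc. The cost is one more secondary analysis, with a rank or composite result that is less direct to read than a mean change.

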### AE Reporting

The investigator was required to promptly notify the sponsor of any serious AEs (SAEs) or significant developments, occurring at any time from the date of informed consent signing, throughout the patient’s scheduled follow-up, and up to 30 days after follow-up completion if the event was likely related to the research. SAEs are defined as events resulting in death, life-threatening situations, hospitalization or prolongation of existing hospitalization, significant or permanent disability, or interventions to prevent such outcomes. Minor AEs are defined as medical occurrences not meeting SAE criteria but which may still relate to study procedures. The sponsor is then responsible for timely reporting of unexpected SAEs and other new occurrences to the ANSM and the relevant ethics committee.

In cases where participants may have been affected, the ethics committee will ensure that the participants are informed of relevant AEs and confirm their ongoing consent.

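### Stopping study treatment is written as study discharge with no 3-month FMA provided for afterwards, so the primary score may be missing for reasons linked to arm and outcome

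*Protocol article*

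**What the plan says.** The exit rule stands under Baclofen Intake Protocol. Because the design is double-dummy and every patient takes capsules, I read it as applying to all three arms. It opens: "Exiting the protocol occurred either by the patient’s deliberate choice or by necessity, according to the investigator's decision". The listed reasons are:

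- "Nonadherence to study conditions: poor compliance with the treatment, unauthorized use of other medications"
- "Uncontrolled painful spasticity despite the use of class I and II analgesics"
- "Occurrence of a serious adverse effect or event"

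It adds: "Premature discharge may be warranted in the event of a clinically significant adverse effect, such as mental confusion, severe sedation". Further examples are swallowing difficulty severe enough to need a feeding tube, a low white-cell count and drug-induced hepatitis. The stated consequence is: "On study discharge, the patient was promptly referred to the investigator for follow-up consultations and ongoing management".

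Other sections bear on this:

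- **Permitted Care During the Trial** names one event, anticoagulation started after the injection, that does not require withdrawal from the study.
- **Data Collection and Management** asks that a discontinuation and its reasons be documented.
- **Primary Outcome** is the FMA change from V0 to V2, at 3 months.
- **Statistical Methods** limits the modified intention-to-treat set to patients with at least one evaluation after randomization.
- **Methods to Handle Missing Data** imputes missing FMA scores by CopyMean, with details settled once the missing-data pattern is known.

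**The concern.** The article has no status for a patient who has stopped treatment but is still followed for outcome. A site working from this text could discharge such a patient to clinical care and not measure FMA at V2.

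The exit reasons are the same for all arms on paper, but they could plausibly fall unevenly. Sedation is the effect that the baclofen escalation rule itself anticipates. Uncontrolled painful spasticity is more plausible without an active antispastic drug. The serious-event reason does not require a link to the drug, and AE Reporting counts "hospitalization or prolongation of existing hospitalization" as serious in a trial that recruits inpatients.

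The trial asks which treatment leaves patients with better motor recovery at 3 months, and its hypothesis is that baclofen may hinder recovery. Patients who tolerate a treatment badly are part of that answer. If their V2 scores are absent, the primary comparison drifts towards patients who tolerated what they were given.

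**Working it through.** **1. What happens to an early exit.** Capsules start at 10 mg and rise by 10 mg every 4 days to 60 mg: 5 steps × 4 days = 20 days without setbacks. V1, the first scheduled evaluation after allocation, is at 1 month. A patient discharged during escalation therefore leaves before V1. Unless an unscheduled evaluation counts, that patient is outside the modified intention-to-treat set and is not imputed within it.

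**2. What happens to a later exit.** A patient who leaves after V1 stays in the set, and a missing V2 score is imputed by CopyMean. The imputation must work from scores that were observed. The article describes no analysis in which leavers are assumed to do worse, or in which the reason for exit plays a part.

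**3. The plan's own allowance for loss.** The amended size is 85 per main arm, said to include 10% loss. Inputs: difference 13, SD 30, two-sided 5%. The article does not restate the power for the amendment.

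- n = 2 × (1.960 + 0.842)² × 30² / 13² = 84 per arm at 80% power, and 84 / 0.90 = 94 with 10% loss.
- At 85% power the figures are 96 and 107.

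So 85 corresponds to 80% power with no loss. With 179 randomized and an assumed exact 2:2:1 split, each main arm has 179 × 0.4 = 71.6. Power for 13 points, Φ(13 / (30 × √(2/n)) − 1.96), is 73.7% if every V2 score is kept and 69.1% if 10% are lost (n = 64.4). This is a separate matter, but it shows that there is no reserve for lost scores.

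**4. Illustration of bias.** Everything here is assumed, since the article gives no exit rates or outcomes by arm. Let d_T and d_B be the proportions without V2 on toxin and baclofen, and let leavers gain L points less than completers in the same arm, with L equal in both. Completers then overstate their arm's mean gain by d × L, so the completer difference is shifted by (d_T − d_B) × L.

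| Exit difference | L | Shift in points | Share of 13 |
|---|---|---|---|
| 5 percentage points | 10 | 0.05 × 10 = 0.5 | 4% |
| 15 percentage points | 20 | 0.15 × 20 = 3.0 | 23% |

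The toxin-baclofen difference is understated if exits are more frequent on baclofen and overstated if more frequent on toxin. With equal exit proportions the shift is zero. It is also zero if V2 is measured after exit and used. This is a complete-case formula and does not model CopyMean.

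**The case against.** The strongest reply is that nothing says V2 is omitted after exit. Discharged patients go back to the investigator, who also runs the study visits, and a condensed article may leave the details to the full protocol. This stands in part. A reader might infer that the V2 scores of leavers are lost; the article supports only that they may be. It does, however, state a rule, name the status as study discharge and exempt just one event from withdrawal, so this is more than silence.

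Other limits also stand:

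- Exit is at the investigator's decision, and discharge for an adverse effect is discretionary. It would be wrong to read that every serious event ends participation.
- Excess sedation during escalation leads first to a lower dose level: "After 2 unsuccessful attempts to increase the dosage, the last tolerated dosage was maintained throughout the study". Ordinary sedation therefore keeps a patient in the trial, and only severe sedation is named as a possible ground for discharge.
- A nonadherent patient with one evaluation after randomization remains in the modified intention-to-treat set, and FMA gaps are imputed. Leaving is not automatic removal from the analysis.

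Two stronger claims are tempting but unsupported: that the exit reasons are common in the ordinary course of stroke, and that leavers are those in whom the treatments differ most. No figure in the article backs either.

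On remedy, inclusion ended in July 2020, so no new assessment is possible. Scales are entered directly in the observation logbooks, so hospital charts may hold little FMA, and the blinding of any unplanned assessment would need checking.

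**Conclusion.** The point holds in a limited form. The exit rule makes stopping treatment a discharge from the study and provides no V2 FMA afterwards, so the primary score may be missing for reasons plausibly related to arm and outcome. Neither the analysis set nor the imputation removes this: exits before V1 can drop out, and later ones depend on scores observed before they left.

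Direction and size are not determined. A reader might infer that the toxin-baclofen difference is necessarily understated; that requires more exits on baclofen, which no figure shows. The 0.5 to 3.0 points are an illustration resting on assumed exit differences, an assumed equal shortfall in both arms and a complete-case comparison. They are not an estimate for the planned analysis. If V2 was in fact collected after exit and is used in the randomized arm, the problem largely disappears and one sentence settles it.

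**What to change.** Separate exit from study treatment from exit from the study, without changing when or why treatment stops, so that only withdrawal of consent ends outcome follow-up. For this completed trial, before the database is frozen (or, if that has happened, as a dated addition before the blind is lifted):

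1. State whether V2 was carried out after exit. Identify every FMA recorded at or near V2 in patients who exited, and include it in the primary analysis in the randomized arm, noting whether the assessor was blinded.
2. Add to CopyMean a delta-adjusted or tipping-point analysis, with the shortfall varied separately by arm. It should cover all randomized toxin and baclofen patients without a V2 score, including those who exited before V1.
3. Report exits by coded arm and reason beside the primary result. Fix the range of shortfalls before this table is made, because reasons such as sedation could hint at an arm's identity.

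The cost is a search of logbooks and, where useful, charts across 18 centers, which may yield little, plus modest analysis work. The estimate will then include some time off treatment, which suits a question about the consequences of choosing a treatment but should be stated.
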